**Methods and analysis:**

We will recruit postgraduate orthopaedic surgeons-in-training in the first 3 years (of 8) of the specialist training programme. Participants will be block randomised and allocated to either cadaveric simulation or standard ‘on-the-job’ training, learning three common orthopaedic procedures, each of which is a substudy within the trial. The procedures are (1) dynamic hip screw, (2) hemiarthroplasty and (3) ankle fracture fixation. These procedures have been selected as they are very common procedures which are routinely performed by junior surgeons-in-training. A pragmatic approach to sample size is taken in lieu of a formal power calculation as this is novel exploratory work with no a priori estimate of effect size to reference. The primary outcome measure is the technical success of the surgery performed on patients by the participating surgeons-in-training during the follow-up period for the three substudy procedures, as measured by the implant position on the postoperative radiograph. The secondary outcome measures are procedure time, postoperative complication rate and patient health state at 4 months postoperation (EQ-5D—substudies 1 and 2 only).

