#### Substudy 2: hemiarthroplasty

Primary outcomeLeg length discrepancy (mm).Secondary outcomes (in order of importance).Femoral stem alignment (degrees off neutral).Cement mantle quality (Barrack grade score).Femoral offset change relative to native hip (mm).

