#### Substudy 3: ankle fracture fixation

Primary outcomeMedial clear space (mm).Secondary outcomesLateral malleolar displacement (mm).Tibiofibular clear space (mm).Talocrural angle (degrees).Medial malleolar displacement (mm).

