### Statistical analysis plan

Baseline data including completed months of training and number of prior procedures performed will be summarised and compared between the two arms of the study. A CONSORT chart showing the flow of participants through the study will be produced. The three taught procedures (substudies 1–3) will be analysed and reported individually.

The main analysis will investigate and report differences between the two groups with respect to the implant positions (as measured from radiographs), the procedure times, the intraoperative radiation dose to the patient, and patient outcomes, as measured by postoperative complications and health state at 4 months postoperation (hip fractures only).

Statistical tests will be two-sided and considered to demonstrate a significant difference when p<0.05. Temporal trends by group for implant position, procedure time and radiation dose will be presented. Linear mixed-effects models will be fitted to allow for within-surgeon correlation between repeated observations (surgeon clustering as a random effect), and to adjust for important covariates such as patient condition, age and surgeon experience. These will be summarised by plotting individual learning curves, and then modelled to estimate the overall learning curves for the two arms of the study.

Descriptive statistical analyses of between-group comparisons will be presented for complication rate and health state, with temporal analysis of the latter being reported if appropriate and feasible. The statistical analysis will be supervised and checked by a senior medical statistician at Warwick University.

In the event of missing data, statistician advice will be sought on multiple imputation.

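### Talocrural angle and femoral offset change can err in either direction, but are to be compared as measured in linear mixed models, which test a shift in the mean rather than accuracy

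*Protocol article*

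**What the plan says.** The abstract (Methods and analysis) names the construct: "The primary outcome measure is the technical success of the surgery performed on patients by the participating surgeons-in-training", as judged from implant position on the postoperative radiograph. The section on radiographic outcomes presents the substudy lists as the definitions of the measurements.

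- **Hemiarthroplasty (substudy 2).** The primary outcome is leg length discrepancy in mm, with no sign convention. The last-ranked secondary outcome is "Femoral offset change relative to native hip (mm". Stem alignment is given as degrees away from neutral.
- **Ankle fixation (substudy 3).** One secondary outcome is "Talocrural angle (degrees", with no reference angle and no mention of deviation.
- **DHS (substudy 1).** The primary outcome is tip-apex distance in mm.

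The Statistical analysis plan section then compares "differences between the two groups with respect to the implant positions (as measured from radiographs". On the method it says "Linear mixed-effects models will be fitted to allow for within-surgeon correlation between repeated observations", with surgeon as a random effect, covariate adjustment and an estimated learning curve for each arm. The significance rule is "Statistical tests will be two-sided and considered to demonstrate a significant difference when p<0.05".

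**The concern.** A linear mixed model compares means. A lower mean is a better result when the measurement has one good direction, as tip-apex distance does. It need not be better when the best value lies inside the range and the surgeon can miss on either side.

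The angle and the offset change are of that second kind. One patient with too much offset and another with too little average to a perfect result. Training that tightens the scatter around the target leaves the group mean, and the mean learning curve, where they were. Such a gain would be reported as no difference. Conversely, two arms that miss by the same amount in opposite directions would be reported as different. In neither case does the p-value bear on technical success.

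**Working it through.** **The plan's own figure.** There is no power calculation to reproduce. The sample size is capacity arithmetic: 16 places × one course = 16 per arm, 32 in all.

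**Inputs from the protocol.** 16 surgeons per arm (a maximum), two-sided 5%, surgeon as random effect.

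**Assumed inputs (the protocol gives none).** Normal errors around the target, control SD 8 mm, m = 5, 10 or 20 operations per surgeon, ICC 0, 0.05 or 0.1. Only the ratio of the SDs and the ratio of bias to SD drive the results, so they carry over to an angle in degrees.

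**Method.** 10,000 simulated trials per setting, with a t-test on surgeon means (30 df, critical value 2.042). With balanced data this is equivalent to the group contrast of a random-intercept model. Each data set was analysed as signed values and as absolute deviation.

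**Formulas.**
- Variance of a surgeon's mean (signed): V = SD² × [ICC + (1 − ICC)/m].
- SE of the arm difference: √(2V/16).
- Mean absolute error with bias μ: SD × √(2/π) × exp(−μ²/(2 SD²)) + μ × [1 − 2Φ(−μ/SD)].

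**Case A: accuracy improves, no bias (SD 8 to 6 mm, both means on target).** Mean absolute error falls from 8 × 0.798 = 6.38 mm to 6 × 0.798 = 4.79 mm. The signed means are equal, so the signed test can reject only at its 5% level.

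**Case B: equal accuracy, opposite bias (−2 v +2 mm, SD 8 in both).** Mean absolute error is 6.58 mm in both arms. At m = 5 and ICC 0.1, V = 64 × (0.1 + 0.9/5) = 17.92, SE = √(2 × 17.92/16) = 1.50, and 4/1.50 = 2.67, which gives 73% rejection on the signed scale.

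**Case C: training removes a constant bias (+3 to 0 mm, SD 8 in both).** At m = 10 and ICC 0.05, V = 64 × (0.05 + 0.095) = 9.28, SE = 1.077, and 3/1.077 = 2.79, which gives 77% power on the signed scale. Mean absolute error falls only from 6.83 to 6.38 mm, and the absolute test has about 11%.

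Rejection rates, each range taken over ICC 0 to 0.1:

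| Operations per surgeon | A signed | A absolute | B signed | B absolute | C signed | C absolute |
|---|---|---|---|---|---|---|
| 5 | 5% | 62–64% | 73–86% | 5% | 50–64% | 8–9% |
| 10 | 5% | 88–90% | 88–99% | 5% | 65–90% | 11–12% |
| 20 | 5% | 99% or more | 95–100% | 5% | 76–100% | 15–19% |

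A smaller gain gives a smaller gap. With the SD cut by 10% (8 to 7.2 mm; m = 10, ICC 0.05), power is about 5% signed and 23% absolute.

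**Positive distances.** For a lower-is-better distance such as tip-apex distance, the value and its absolute value are the same, so the two analyses are identical.

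**The case against.** **The protocol never says that signed values enter the model, and coding of derived variables is often left to a full protocol or SAP that is not shown.** This stands for leg length discrepancy: in ordinary use a discrepancy is a size, and on that reading a difference in means does measure accuracy. It has less force for the other two. The text presents its lists as definitions and gives one item as a raw angle and the other as a change. Taken literally, those are what the models would analyse.

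**No null hypothesis is stated.** Correct. The announced comparison is of implant positions, and arms at −2 and +2 mm do differ in position. A reader might call Case B an inflated type I error. The documents do not support that, because a null of equal accuracy is only inferred from the abstract's description of the primary outcome. Case B shows a mismatch with the construct, not a breach of a stated error rate.

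**Absolute deviation is not always the more powerful scale.** Correct, as Case C shows. Using it alone would largely hide the correction of a systematic bias, so the signed difference has to be kept with its confidence interval.

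**The trial is exploratory and the affected outcomes are secondary.** This limits the consequences. It does not make a cancelling mean a measure of accuracy.

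**Conclusion.** The point holds for talocrural angle and femoral offset change as the protocol defines them. Under the stated assumptions, a one-quarter reduction in scatter would be picked up about 5% of the time on the signed scale, against 62% to over 99% on absolute deviation. The sizes rest on assumed SDs, ICCs and operation counts, on normal errors and on balanced data. The direction of the problem does not depend on those figures. It does depend on the target lying inside the range of values, which is read from the nature of the measurements because the protocol names no target angle.

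A reader might infer that the hemiarthroplasty substudy cannot answer its primary question. The document does not support this. The point would reach leg length discrepancy only if that is recorded with sign, and the text is silent. Nor does it touch tip-apex distance, and stem alignment already reads as a deviation. The linear mixed model itself is not at fault. What needs changing is the scale of the outcome that goes into it.

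**What to change.** In the hemiarthroplasty and ankle outcome lists, and again in the Statistical analysis plan section, define the analysed outcome as absolute deviation from target:

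- the absolute value of femoral offset change;
- the absolute value of leg length discrepancy, which also settles its sign;
- the absolute value of talocrural angle minus a reference angle that is fixed before allocation is revealed.

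Fit the same mixed models and learning curves to these variables, transformed if skewed. Report the signed mean difference with its confidence interval as a supporting analysis of systematic bias.

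The cost is wording and one derived variable per outcome, using the same radiographs and measurements. There are three downsides: absolute deviations are right-skewed, a reference angle must be chosen in advance, and power on the main scale is lower when the training effect is removal of a constant bias.

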#### Substudy 1: DHS

Primary outcomeTip–apex distance (mm).Secondary outcomes (in order of importance)Lag screw position in the femoral head (defined by Cleveland Zones).Plate flush to lateral femoral cortex (binary Y/N).Eight cortex hold for plate screws (binary Y/N).

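### Linear mixed models are the only model named for implant position, but four of the 13 radiographic outcomes, all secondary, are categorical and need a model matched to their scale

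*Protocol article*

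**What the plan says.** In the protocol article, the Radiographic outcomes section introduces implant position as the thing measured on the films, and says the measurements depend on the operation. Three lists follow, one per substudy. Most entries carry a unit of millimetres or degrees. Four do not:

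- Substudy 1 (DHS): "Lag screw position in the femoral head (defined by Cleveland Zones", "Plate flush to lateral femoral cortex (binary Y/N" and "Eight cortex hold for plate screws (binary Y/N". These are all of the DHS secondary outcomes, and the list is ranked by importance with lag screw position first.
- Substudy 2 (hemiarthroplasty): "Cement mantle quality (Barrack grade score".

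The Statistical analysis plan section says that the main analysis will report "differences between the two groups with respect to the implant positions (as measured from radiographs", without dividing the measures by scale. It sets the test rule: "Statistical tests will be two-sided and considered to demonstrate a significant difference when p<0.05". It adds that "Temporal trends by group for implant position, procedure time and radiation dose will be presented", and the next sentence gives the model: "Linear mixed-effects models will be fitted to allow for within-surgeon correlation between repeated observations". That model also carries the covariate adjustment and the estimated learning curves for each arm. Only complication rate and health state are set aside for descriptive analysis.

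**The concern.** The one model family in the plan assumes an outcome for which a mean, and a straight-line change in that mean, make sense. A Cleveland zone is a location in the femoral head, so its number is a label. A yes/no item has a mean (a proportion), but one bounded at 0 and 1. A Barrack grade is ordered, but nothing in the document says that its steps are equal.

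Two things are at stake. The top-ranked DHS secondary outcome cannot give an interpretable arm difference if its codes enter the stated model. Any usable analysis needs a recoding that the article does not give. The Blinding section blinds only the assessment of the images, so a recoding chosen late could be chosen with knowledge of the arms. Second, defining the early learning curve is a stated objective, and learning curves are where a linear model serves yes/no outcomes worst.

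**Working it through.** The plan gives no figure on this point to reproduce, so the check has four parts.

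**1. Count.** From the three substudy lists:

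| Substudy | Outcomes | Not continuous | Primary |
|---|---|---|---|
| 1 DHS | 4 | 3 (1 nominal, 2 binary) | tip–apex distance, mm |
| 2 Hemiarthroplasty | 4 | 1 (ordinal) | leg length discrepancy, mm |
| 3 Ankle | 5 | 0 | medial clear space, mm |
| Total | 13 | 4 | 0 of 3 affected |

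4/13 = 31%.

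**2. Cleveland zone.** The article gives no zone counts, so these are invented: nine zones (assumed) and 160 operations per arm. Arm A has 3, 5, 8, 8, 88, 16, 8, 16, 8 and arm B has 3, 5, 16, 8, 80, 8, 8, 24, 8. The arms differ only in zones 3 and 8 (A has 8 fewer in each) and zones 5 and 6 (A has 8 more in each). If zone k carries label L_k, the difference in means is

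(8/160) × (L5 + L6 − L3 − L8) = 0.05 × (L5 + L6 − L3 − L8).

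- Labels 1 to 9 in order: 0.05 × (5 + 6 − 3 − 8) = 0.
- Labels 1, 7, 6, 5, 4, 2, 8, 9, 3: 0.05 × (4 + 2 − 6 − 9) = −0.45.
- Labels 8, 6, 3, 5, 9, 1, 7, 4, 2: 0.05 × (9 + 1 − 3 − 4) = +0.15.

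The same data give a zero, negative or positive effect according to the numbering alone.

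**3. Yes/no outcomes, arm comparison.** A linear mixed model with a surgeon random intercept was simulated with no true arm effect. From the article: 16 surgeons per arm (the stated maximum) and two-sided 0.05. Assumed: 5 or 15 operations per surgeon, success for a typical surgeon of 0.5, 0.8 or 0.95, surgeon SD on the logit scale of 0.3, 0.7 or 1.2, equal numbers of operations, and no covariates. There were 18 settings with 20,000 runs each (simulation SE about √(0.05 × 0.95/20,000) = 0.0015).

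| Setting | Normal reference | t, 30 df |
|---|---|---|
| Lowest (0.95, 5 operations, SD 0.7) | 0.042 | 0.032 |
| Highest (0.5, 15 operations, SD 0.7) | 0.062 | 0.053 |

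The arm comparison is near nominal, or conservative.

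**4. Yes/no outcomes, learning curve.** Suppose (illustrative rates) that one arm starts at 80% and the other at 92%, and both gain one unit on the logit scale over a period.

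- 80%: logit 1.386, rising to 2.386, which is 91.6%. Gain 11.6 points.
- 92%: logit 2.442, rising to 3.442, which is 96.9%. Gain 4.9 points.

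The logit-scale gains are identical, but a linear model shows unequal slopes because one arm is nearer the ceiling. Extended for one more period, the straight lines reach 91.6 + 11.6 = 103.2% and 96.9 + 4.9 = 101.8%. The logit curves reach 96.7% and 98.8%.

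For Barrack grade no calculation is needed: a linear model on grade numbers treats every one-grade step as equally large.

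**The case against.** The strongest reply is that the model sentence lists no outcomes. The three named outcomes stand in the sentence before it, which is about presenting trends, and nothing says that zone numbers will be averaged. On that view the article is merely silent on four secondary outcomes, and a condensed article may leave such detail to a full plan.

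Part of this stands: the assignment is inferred. But the article uses implant position as its collective term for every listed radiographic measure, puts implant positions in the main analysis as a whole, names one model, and exempts only complication rate and health state. The natural reading is that the linear model covers all the radiographic measures. That makes it a stated choice that fits four of them badly, and not simply an omission.

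A reader might go further and infer that all four analyses are invalid. The documents and the check do not support that. A linear model on a yes/no item estimates a risk difference, and its simulated error rate was close to 0.05. For Barrack grade, equal spacing is a debatable assumption and not an invalid analysis. Only Cleveland zone fails outright. The simulation had equal cluster sizes and no covariates, so it does not clear the learning-curve slopes.

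A reader might also want procedure time, fluoroscopy time and dose log-transformed. The article gives no distribution for any of them, and the choice between mean differences and ratios is one of estimand. No fault is shown there.

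Finally, mixed logistic models can meet sparse cells or fail to converge with at most 32 surgeons and success near 100%. That stands, and calls for a stated fallback.

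**Conclusion.** The point holds at a moderate level: it should be fixed, but it does not threaten the primary analyses. Four of 13 radiographic outcomes (31%), all secondary and including all three DHS secondaries, fall under a model that does not suit their scale. The defect is complete for Cleveland zone, confined mainly to learning curves for the two yes/no items, and a matter of assumed spacing for Barrack grade. Tip–apex distance, leg length discrepancy and medial clear space are untouched, as is the whole radiographic set for ankle fixation.

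The conclusion rests on reading implant position as covering every listed radiographic measure. The zone counts, success rates and operations per surgeon used above are assumptions. They show the mechanism and do not predict the size of any error in this trial.

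**What to change.** State a model for each type of scale:

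- Millimetre and degree measures: linear mixed models, as now.
- Plate flush and eight-cortex hold: mixed logistic regression with a surgeon random intercept, with learning curves fitted on the logit scale. Name a fallback for sparse data or non-convergence. One option is the linear risk difference for the arm comparison only, which the simulation supports.
- Barrack grade: a mixed ordinal model with a surgeon random intercept.
- Cleveland zone: fix a grouping of zones before outcome data are seen by arm, analyse the resulting yes/no variable by mixed logistic regression, and tabulate the full zone distribution by arm.

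The cost is a few sentences of analysis-plan text and no new data. The downsides are small: possible sparse-cell or convergence problems with at most 32 surgeons, which the fallback covers, and some loss of detail from grouping zones, which the table makes good.

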## Ethics and dissemination

Master-apprentice ‘on-the-job’ training for surgeons is the current training standard in the UK,^10 16^ and therefore the control arm of the study reflects usual practice. The cadaveric simulation training intervention is an experimental educational intervention and does not expose trial participants to any substantial risks of harm. The trial results will be reported in accordance with the CONSORT statement, and disseminated through publication in peer-reviewed journals and conferences. The results of the trial will be presented to Health Education England and the Royal Surgical College. The dataset, statistical code and technical appendices will be made available on request to the corresponding author. The study was approved by the NHS Research Authority South Birmingham Research Ethics Committee (15/WM/0464).
